### Randomization

Computerized block randomization for allocation of treatment group, stratified for center and for Hinchey 1a and 1b, will take place after all inclusion and exclusion criteria have been verified and informed consent has been obtained. A standardized case record from (CRF) will be used. This CRF is partially web-based via a secured internet module. A minimum of 10% of the CRF data will be verified with source data by an independent audit.

### Sample size calculation and date analysis

A non-inferiority design was chosen. Time-to-full recovery in the liberal strategy arm must not exceed a clinically relevant difference of more than 5 days compared with the conservative strategy. When this condition is fulfilled, the potential advantages of the liberal (non-antibiotic) strategy become dominant: patient well being when the need of hospital admission can be avoided, less costs, less antibiotic resistance and less other side effects. The study must have the power (superiority) to detect a difference in time-to-full recovery of 5 days.

The median time-to-full recovery is 21 days based on the National Dutch Hospital Registry data with an average of 7 days admission and an assumed additional median 14-day out-patient period to full recovery. To reject the null-hypothesis of a difference in time-to-full recovery of 5 days or less, using a time-to-event analysis with a power of 85% at a confidence level of 95%, an accrual period of 730 days and a follow-up period of 180 days, at least 264 patients need to be included in each treatment arm. With an estimated one percent of the trial patients lost to follow-up, a total 533 patients is needed.

The primary endpoint is time-to-full recovery. Kaplan-Meier curves depicting the proportion of patients with full recovery since randomisation will be constructed for both strategies. The log rank test will be used to test for superiority of one strategy compared with the other. Testing for non-inferiority will be done by calculating the hazard ratio for the liberal strategy compared with the conservative strategy using Cox regression. We will calculate a one-sided 95% confidence interval for this ratio to determine whether it reaches outside the hazard ratio belonging to an equivalence limit of a difference of 5 days in median survival time.

For other endpoints data will be compared by the Student's t test, Wilcoxon rank sum test, Chi square test or Fischer exact test as appropriate. In superiority tests a two-tailed P value ≤ 0.05 will be considered statistically significant, whereas one-sided tests will be performed in non-inferiority testing. The main analyses will be based on the intention to treat principle. Predefined subgroup analyses to investigate whether treatment effects are different in subgroups will be performed for Hinchey classification 1a versus 1b and for participating center.

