**Methods:**

A randomized multicenter pragmatic clinical trial comparing two treatment strategies for uncomplicated acute diverticulitis. I) A conservative strategy with antibiotics: hospital admission, supportive measures and at least 48 hours of intravenous antibiotics which subsequently are switched to oral, if tolerated (for a total duration of antibiotic treatment of 10 days). II) A liberal strategy without antibiotics: admission only if needed on clinical grounds, supportive measures only. Patients are eligible for inclusion if they have a diagnosis of acute uncomplicated diverticulitis as demonstrated by radiological imaging. Only patients with stages 1a and 1b according to Hinchey's classification or "mild" diverticulitis according to the Ambrosetti criteria are included. The primary endpoint is time-to-full recovery within a 6-month follow-up period. Full recovery is defined as being discharged from the hospital, with a return to pre-illness activities, and VAS score below 4 without the use of daily pain medication. Secondary endpoints are proportion of patients who develop complicated diverticulitis requiring surgery or non-surgical intervention, morbidity, costs, health-related quality of life, readmission rate and acute diverticulitis recurrence rate. In a non-inferiority design 264 patients are needed in each study arm to detect a difference in time-to-full recovery of 5 days or more with a power of 85% and a confidence level of 95%. With an estimated one percent of patients lost to follow up, a total of 533 patients will be included.

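### With exponential recovery times, the stated inputs give 264 patients per arm about 79% power for non-inferiority, not 85%; the superiority claim has no direction and the null hypothesis is worded backwards

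*Protocol article*

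**What the plan says.** The section headed Sample size calculation and date analysis sets a non-inferiority aim in the slower direction: "Time-to-full recovery in the liberal strategy arm must not exceed a clinically relevant difference of more than 5 days compared with the conservative strategy". It gives one median and names no arm for it: "The median time-to-full recovery is 21 days based on the National Dutch Hospital Registry data with an average of 7 days admission", plus an assumed 14-day out-patient median. The non-inferiority analysis is a Cox model: "We will calculate a one-sided 95% confidence interval for this ratio". The bound is then compared with the limit, to see "whether it reaches outside the hazard ratio belonging to an equivalence limit of a difference of 5 days in median survival time". The numerical hazard ratio is not given.

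The 264 per arm is then justified with this hypothesis: "To reject the null-hypothesis of a difference in time-to-full recovery of 5 days or less". For the remaining inputs, the section describes the calculation as "using a time-to-event analysis with a power of 85% at a confidence level of 95%, an accrual period of 730 days"; follow-up is 180 days. One percent loss to follow-up brings the total to 533.

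The same section adds a superiority requirement: "The study must have the power (superiority) to detect a difference in time-to-full recovery of 5 days". Superiority is to be tested by log-rank at two-tailed 5%. The abstract's Methods paragraph, in a sentence that calls the design non-inferiority, says that "264 patients are needed in each study arm to detect a difference in time-to-full recovery of 5 days or more".

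**The concern.** There are three difficulties.

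- **The size does not follow from the inputs.** A median of 21 days, a limit of 26 days, a one-sided 5% test and 85% power lead to a larger number than 264 under the standard conversion from medians to a hazard ratio.
- **One number is given two justifications.** The text presents 264 both as a non-inferiority size and as a size that detects a 5-day difference. These are different tests with different error rates, and the direction of the superiority effect is not stated.
- **The null hypothesis is reversed.** Rejecting a difference of 5 days or less would show a difference of more than 5 days, the opposite of the stated aim. The wording fits neither planned test: the non-inferiority null is a delay of 5 days or more, and the log-rank null is no difference.

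At stake is what a reader may conclude from an inconclusive result. If the strategies are truly equal, an advertised 15% risk of failing to show non-inferiority could be about 21%.

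**Working it through.** **Inputs.** All come from the sample-size section: median 21 days; limit 5 days slower, so 26 days; one-sided 5% for non-inferiority; two-sided 5% for superiority; power 85%; 180 days of follow-up; 264 per arm (528 in total); 1% loss. One assumption is added: exponential (constant-hazard) recovery times, so that a ratio of medians gives a hazard ratio.

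**Loss to follow-up.** 528/0.99 = 533.3. The stated 533 reproduces, so the discrepancy lies in the 264.

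**Censoring.** The probability of no recovery by day 180 is 2^(-180/21) = 0.26% at median 21 and 2^(-180/26) = 0.82% at median 26. Almost every patient contributes an event, so the accrual and follow-up inputs hardly matter.

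**Non-inferiority, recoveries needed.** Limit HR = 21/26 = 0.808; ln(0.808) = -0.2136. Schoenfeld:

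events = 4 × (1.645 + 1.036)² / 0.2136² ≈ 630.4, so 631 (Freedman: 636).

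That is about 316 per arm if all recover, and about 317 after allowing for those unrecovered at day 180.

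**Non-inferiority, power at 264 per arm, true HR 1.**

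power = Φ(√(528/4) × 0.2136 − 1.645) = Φ(2.454 − 1.645) = 79.1%.

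With 525 recoveries it is 78.9%. Simulating the planned Cox bound (264 per arm, censoring at 180 days, 6,000 runs) gives 78.3%.

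**Superiority, two-sided 5%.**

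- *5-day delay, 26 versus 21 days:* events for 85% = 4 × (1.960 + 1.036)² / 0.2136² ≈ 787.3, so 788, about 396 per arm after censoring. At 528 events, power = Φ(2.454 − 1.960) = 68.9% (simulation 68.7%).
- *5-day gain, 16 versus 21 days:* ln(16/21) = -0.2719; 486 events, about 243 per arm. At 528 events, power = Φ(11.489 × 0.2719 − 1.960) = 87.8% (simulation 87.1%).

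**Other routes to 264 at 85% power.**

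| Reading | Per arm needed |
|---|---|
| 26 v 21, one-sided 5% | 317 |
| 26 v 21, two-sided 5% | 396 |
| 16 v 21, two-sided 5% | 243 |
| 16 v 21, one-sided 5% | 195 |
| Linear-scale exponential test, both medians 21, one-sided (not the planned test) | 254 |

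None gives 264. Working backwards, 264 per arm at one-sided 5% and 85% power corresponds to a limit HR of exp(−2.681 × √(2/264)) = 0.792. With a 21-day median that is a limit of 21/0.792 = 26.5 days; with a 5-day limit it fits a reference median of about 19 days (19/24 = 0.792).

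**The case against.** The strongest objection is that the article never says hazards are constant. A Cox model needs only proportional hazards, and the hazard ratio that corresponds to 26 versus 21 days depends on the shape of the recovery curve. The result is sensitive to this:

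- With Weibull times of shape k, the limit is (21/26)^k. At k = 1.09 it is 0.792 and the power is about 85%; at k = 1.2 the power is about 90%.
- Exponential recovery that begins on day 2 gives a limit of 19/24, which also matches 264.
- The article builds its 21 days from an admission phase and an out-patient phase, which does not suggest a constant hazard. As an extreme illustration, 7 fixed days followed by an exponential phase with median 14 gives a limit of 14/19 = 0.737 and about 97% power.

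These shapes are assumptions too, and the article states none of them. The objection stands to this extent: 79% is conditional. A reader might infer that no set of inputs can yield 264, or that the design is certainly underpowered; the document supports neither. A condensed article may also leave the distribution and software to the full protocol. But it does print the inputs, the result and the null hypothesis, and these do not fit together under the usual conversion.

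Two further objections stand. The superiority power is not simply 69%: for a 5-day gain, 264 per arm exceeds 85%, and the text does not say that the 85% belongs to superiority. And the reversed null does not alter the analysis, because the aim is stated in the right direction and the operative rule compares a one-sided confidence bound with the limit.

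**Conclusion.** The point holds with its conditions. Assuming exponential recovery times, a 21-day reference median and truly equal arms, 264 per arm gives about 79% power for the planned non-inferiority test, against 85% stated; 85% needs about 317 per arm. Neither censoring nor the loss allowance explains the gap, and none of the exponential log-rank or Cox readings tried reproduces 264. A modest departure from exponential times would close the gap, so the defect is a power figure that cannot be recovered from the printed inputs, not proof that the trial is too small.

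The superiority statement is incomplete without a direction: about 69% for a 5-day delay, about 88% for a 5-day gain. On the first, the log-rank test would miss a real 5-day delay about 31% of the time.

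The null hypothesis is wrong as written. A reader might infer that the wrong hypothesis would be tested, but the stated confidence-interval rule shows otherwise. Type I error, the 5-day limit and the decision rule are unaffected.

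**What to change.** In the sample-size section and the abstract:

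1. Either state the recovery-time distribution, reference median and limit hazard ratio that give 264 per arm at 85% power, or restate the power as about 79% for non-inferiority at a limit HR of 0.81 (one-sided 5%, true HR 1), assuming exponential recovery times.
2. Print the numerical limit hazard ratio in either case, because the primary conclusion is judged against it.
3. Give superiority power with its direction and the same assumption: about 69% for 26 versus 21 days and about 88% for 16 versus 21 days, two-sided 5%.
4. Write the hypotheses as H0: liberal minus conservative is 5 days or more; H1: less than 5 days.
5. In the abstract, change the claim about detecting a difference to one about excluding a delay of 5 days or more.

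The cost is wording only. If the second option in item 1 is taken, the stated power becomes less favourable. No extra patients are required, and the planned analysis does not change.

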### Study outline

Patients will be randomly allocated to one of the following two treatment strategies: Conservative strategy including immediate antibiotic treatment or liberal strategy without antibiotics (supportive measures only). (Table 4).

**Table 4 T4:** Treatment strategies

Conservative strategy with antibiotics	Liberal strategy without antibiotics
- Hospital admission;	- Admission only if discharge criteria are not met;

- Intravenous fluids and at least 48 hours of intravenous antibiotics and subsequently switch to oral antibiotics if tolerated (otherwise continuation i.v.) to complete a full 10-day treatment duration;	- No initial antibiotics;

- Adequate pain relief (VAS < 4);	- Adequate pain relief (VAS < 4);

- Oral intake as tolerated;	- Oral intake as tolerated;

- Daily monitoring.	- Daily monitoring when admitted to the hospital;

-Self monitoring at home after discharge -Out patient follow-up at regular intervals	- Self monitoring at home. - Out patient follow-up at regular intervals

In the conservative strategy, the use of antibiotics will be intravenously for at least 48 hours after which route of administration can be switched to orally if tolerated. Hospital admission in the liberal strategy is needed for patients with nausea and vomiting, in need of intravenous fluids or for patients with excessive pain not properly reacting to oral pain medication.

The interval between start of symptoms of the patient and administration of antibiotics will be registered. Also the period after inclusion and the actual first administration of antibiotics will be registered.

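### The 5-day non-inferiority margin is tested on a hazard ratio that is neither stated nor recoverable from the sample size, so the primary decision threshold is not fixed

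*Protocol article*

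**What the plan says.** All of this stands in the Protocol article, mainly under Sample size calculation and date analysis.

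- Design and margin: "A non-inferiority design was chosen". The margin is on the time scale: "Time-to-full recovery in the liberal strategy arm must not exceed a clinically relevant difference of more than 5 days compared with the conservative strategy".
- Test: "Testing for non-inferiority will be done by calculating the hazard ratio for the liberal strategy compared with the conservative strategy using Cox regression". A one-sided 95% confidence interval for that ratio is then judged by "whether it reaches outside the hazard ratio belonging to an equivalence limit of a difference of 5 days in median survival time".
- Planning median: "The median time-to-full recovery is 21 days based on the National Dutch Hospital Registry data with an average of 7 days admission", to which is added "an assumed additional median 14-day out-patient period to full recovery".
- Size: 264 patients per arm (528; 533 with 1% loss), for 85% power at a confidence level of 95%, with 730 days of accrual and 180 days of follow-up.

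No hazard ratio, conversion formula or distribution of recovery times is given. Kaplan-Meier curves and a log-rank test for superiority are planned. An interval for the difference in medians is not mentioned.

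**The concern.** The clinical margin is in days, the decision is on a ratio, and the link between them is one phrase that fits several numbers. A difference of 5 days in medians corresponds to a hazard ratio only once a control median and a curve shape are chosen. The text does not say whether the median is the 21-day planning value or the one observed in the conservative arm. The 21 days is itself an average stay plus an assumed median, which in general is not the median of the sum, so the observed value may well differ.

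Two things are at stake. The threshold for the primary conclusion could be set after the control curve is seen, in a trial where neither patients nor treating physicians are blinded (Safety monitoring). And even with a fixed ratio, passing the test need not mean that the delay is under 5 days, because the days that a given ratio allows depend on the control curve.

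**Working it through.** **Inputs from the article.** Control median 21 days; margin 5 days; one-sided 5%; power 85%; 528 patients. A hazard ratio (HR) below 1, liberal versus conservative, means slower recovery in the liberal arm.

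**1. The plan's own figure.** With exponential times the limit is m/(m+5) = 21/26 = 0.808, and ln(0.808) = −0.2136. Schoenfeld's formula with 1:1 allocation:

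events = 4 (1.645 + 1.036)² / 0.2136² = 4 × 7.189 / 0.0456 ≈ 631.

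Over 180 days nearly all patients would recover under this model (event probability about 0.995), so this means about 635 patients, against 528 stated. Other readings do not give 528 either:

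| Limit | Sides | Power | Events |
|---|---|---|---|
| 21/26 | one | 85% | 631 |
| 21/26 | two | 85% | 788 |
| 16/21 | one | 85% | 389 |
| 16/21 | two | 85% | 486 |
| 21/26 | one | 80% | about 542 |

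The nearest is the last row, which is not at the stated power. The loss allowance agrees: 528/0.99 = 533.3.

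**2. Working back from 528 events.** The standard error of log HR is √(4/528) = 0.0870.

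- Power at 0.808 with no true difference: Φ(0.2136/0.0870 − 1.645) = 79%.
- Limit implied by 85% power: exp(−(1.645 + 1.036) × 0.0870) = 0.792. With a 21-day exponential median this is 21/0.792 − 21 = 5.5 days.

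**3. Can two readings reverse the verdict?** Take an observed HR of 0.92. The one-sided 95% lower bound is 0.92 × exp(−1.645 × 0.0870) = 0.797, which is below 0.808 (fail) and above 0.792 (pass).

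**4. If the observed control median were used.** Under exponential times with 264 patients, the standard error of the median is √(0.25/264) / (0.5 × ln 2 / 21) = 1.86 days. The range 21 ± 1.96 × 1.86 is 17.3 to 24.7 days, and m/(m+5) then runs from 0.78 to 0.83 through sampling error alone.

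**5. Days allowed by a fixed limit of 0.808.** The shapes and medians other than 21 are assumptions, shown as a range. For Weibull shape k with median 21, days = 21 × ((26/21)^(1/k) − 1). For exponential times with median m, days = 5m/21. The last column is the chance of declaring non-inferiority when the true delay is exactly 5 days (nominal 5%).

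| Control curve | Days allowed | False claim |
|---|---|---|
| Weibull 0.7, median 21 | 7.5 | 18% |
| Exponential, median 28 | 6.7 | 14% |
| Exponential, median 21 | 5.0 | 5% |
| Exponential, median 14 | 3.3 | 0.4% |
| Weibull 1.5, median 21 | 3.2 | 0.2% |

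**The case against.** The strongest reply is that the number follows from the same section. A 21-day median and a 5-day limit give 21/26 = 0.81, nothing says that the observed median will be used, and a journal article commonly leaves the printed decimal to the full protocol. Part of this stands: 0.81 is the most natural reading, and nothing shows an intention to choose the threshold late. But this is more than missing detail. The article states the primary decision rule in a form that admits several thresholds, and its own sample size does not match the natural one.

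A reader might infer that the margin has meaning only under constant hazards. That goes too far. Under proportional hazards, which the Cox model assumes anyway, a 5-day shift has a hazard ratio for any control curve, namely ln 0.5 / ln S₀(median + 5). Only the shortcut m/(m+5) needs exponential times.

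A reader might also infer that the rule would pass delays longer than 5 days. The documents do not support that direction. It needs falling hazards or a control median above 21 days, and no section points to either. What the article does say points the other way. Full recovery requires discharge, and "In the conservative strategy, the use of antibiotics will be intravenously for at least 48 hours", so the early hazard in that arm is close to zero and then rises. With a 2-day lag followed by exponential recovery (median 21), 0.808 allows (21 − 2) × 5/21 = 4.5 days. With two exponential stages (mean stay 7 days, then median 14) it allows about 3.6 days. Both shapes are assumed, and both make 0.808 stricter than 5 days. Nor does the 48-hour rule carry much weight against a 21-day median, since few patients in either arm would plausibly meet every recovery criterion that early.

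**Conclusion.** The concern holds as a badly fixed decision threshold. The limit is not given as a number, the median behind it is not named, and 264 per arm corresponds to 0.792 rather than 0.808 at the stated error rates. These two values give opposite conclusions for an observed hazard ratio between about 0.914 and 0.932 (each limit multiplied by exp(1.645 × 0.0870)). These figures assume exponential times and close to 528 recoveries.

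Separately, a fixed ratio of 0.808 equals 5 days only for a control curve like the planned one. Over the assumed range it allows between 3.2 and 7.5 days. The mismatch runs both ways, and the documents do not show that it favours the liberal strategy. Because the primary conclusion depends on this limit, it should be settled before outcome data are seen.

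**What to change.** 1. State the limit as a number now: non-inferiority is concluded if the lower one-sided 95% bound of the hazard ratio (liberal versus conservative) lies above 21/26 = 0.81. Say that it derives from the 21-day planning median under exponential times and will not be recomputed from observed data.
2. Restate the power as about 79% with 528 events. Keeping 85% at this limit would need about 635 patients, or about 642 with 1% loss.
3. Pre-specify, as a supporting estimate, the Kaplan-Meier difference in medians with a one-sided 95% bootstrap bound. Report it beside the hazard ratio, and qualify any statement that the delay is within 5 days when the bound exceeds 5.

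The third item should not become a second required test without weighing the loss. With a standard error of 1.86 days per arm, that of the difference is 1.86 × √2 = 2.64. With no true difference the bound then falls below 5 days with probability Φ(5/2.64 − 1.645), about 60%, against about 79% for the hazard-ratio test.

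The cost is one extra analysis and a less favourable stated power. The fixed limit is stricter in days if control recovery is faster than 21 days and looser if it is slower. No visit, treatment or data item changes.

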### Endpoints

The primary endpoint is time-to-full recovery within a follow-up period of 6 months. Full recovery is defined by the following criteria: discharged from the hospital (out-patient), normal diet (defined by tolerating solid food and more than 1L of fluid orally), temperature < 38.0°C, and VAS pain score < 4, no use of daily pain medication or back to pre-illness pain medication use, and resuming to pre-illness working activities; as assessed by questionnaires and out-patient clinic visits.

The secondary endpoints are: proportion of patients who develop complicated diverticulitis require surgery or non-surgical intervention; number of days outside the hospital in a 6 months period; direct and indirect medical costs at 6 months follow-up; occurrence of complicated diverticulitis defined as abscess, perforation, stricture and/or fistula; predefined side-effects of initial antibiotic treatment (e.g. antibiotic resistance/sensitivity pattern, allergy); morbidity (e.g. pneumonia, myocardial infarction, urinary tract infection); mortality; readmission rate within 6 months and acute diverticulitis recurrence rates at 12 and 24 months follow-up. Changes in health status and valuation over time will be measured using generic and disease specific quality of life questionnaires (Euro-Qol 5D, Short Form 36 (SF-36) and the Gastro-Intestinal Quality of Life Index (Giqli)) on admission and after 3, 6, 12 and 24 months.

A recurrence is defined as ultrasound- or CT-proven acute diverticulitis after complete resolution of symptoms more than 1 month after initial discharge from hospital. If a patient dies during follow-up, the reason for death will be recorded as related or unrelated to diverticular disease.

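### The four unadjusted tests named for the other endpoints give up precision on quality of life and cannot use partial follow-up for 24-month recurrence

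*Protocol article*

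**What the plan says.** In the protocol article, *Sample size calculation and date analysis* gives the primary endpoint Kaplan-Meier curves, a log rank test and Cox regression. It then disposes of the rest in one sentence: "For other endpoints data will be compared by the Student's t test, Wilcoxon rank sum test, Chi square test or Fischer exact test as appropriate". The qualifier at the end selects among the four tests; it does not add a fifth method.

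Two of the endpoints covered by that sentence have more structure than a two-sample test can use (*Endpoints*):

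- Quality of life: "Changes in health status and valuation over time will be measured using generic and disease specific quality of life questionnaires", namely EQ-5D, SF-36 and GIQLI, taken "on admission and after 3, 6, 12 and 24 months". That is one baseline and four follow-up visits.
- Recurrence: "acute diverticulitis recurrence rates at 12 and 24 months follow-up". It must be proven by imaging and occur "after complete resolution of symptoms more than 1 month after initial discharge from hospital", so each event can be dated.

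Randomization is "stratified for center and for Hinchey 1a and 1b", and the *Discussion* justifies these two factors as the ones that matter most for outcome. The only figure for loss is in the sample-size paragraph: "With an estimated one percent of the trial patients lost to follow-up, a total 533 patients is needed". It belongs to a calculation with 180 days of follow-up.

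**The concern.** This is a choice that the article states, not a silence that a later analysis plan would be expected to fill. Read as written, it leaves collected information unused in two places.

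For quality of life, none of the four tests adjusts for the admission score or for the stratification factors, and each visit has to be tested separately. The stake is precision.

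For recurrence, none of the four tests can use a patient who is followed for part of the 24 months. The analyst must count such a patient as recurrence-free or leave the patient out, and the article gives no rule. The survival methods that would use partial follow-up are named only for the 6-month primary endpoint, where little loss is expected. The stake is a small bias in a longer-term outcome of withholding antibiotics, if loss by 24 months is material or differs between the arms of this unblinded trial.

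**Working it through.** **The plan's own figure.** The article gives no number for the secondary analyses. The one relevant figure is the 1% loss: 2 × 264 = 528, and 528 / 0.99 = 533.3, which agrees with the stated 533. This covers the 180-day design and says nothing about 24 months.

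**Quality of life.** Inputs: 264 per arm and two-sided 5% from the article. The correlation ρ between admission and follow-up scores, and equal standard deviations (SD) at both times, are assumptions. Variances are relative to a t test on follow-up scores alone:

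- t test on change from admission: 2(1 − ρ)
- ANCOVA: 1 − ρ²
- change minus ANCOVA: 2(1 − ρ) − (1 − ρ²) = (1 − ρ)², which is never negative

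Power is shown for an effect that gives the follow-up t test 80% power: (1.96 + 0.84) × √(2/264) = 0.244 SD.

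| ρ | Change variance | ANCOVA variance | Change power | ANCOVA power |
|---|---|---|---|---|
| 0.3 | 1.40 | 0.91 | 66% | 84% |
| 0.5 | 1.00 | 0.75 | 80% | 90% |
| 0.7 | 0.60 | 0.51 | 95% | 98% |

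At ρ = 0.3 the change score does worse than leaving the baseline out.

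**Recurrence.** The true 24-month risk p and the loss L are assumptions. With constant rates λ = −ln(1 − p)/24 and μ = −ln(1 − L)/24, and loss independent of recurrence, counting every lost patient as recurrence-free gives

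observed risk = λ/(λ + μ) × [1 − (1 − p)(1 − L)].

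Example: p = L = 0.20 gives 0.5 × (1 − 0.64) = 0.18, which is 2.0 points too low.

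| True risk | Error at 1% loss | At 10% | At 20% |
|---|---|---|---|
| 5% | −0.02 | −0.25 | −0.51 |
| 10% | −0.05 | −0.50 | −1.02 |
| 15% | −0.07 | −0.74 | −1.52 |
| 20% | −0.10 | −0.98 | −2.00 |

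(percentage points)

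Unequal loss of 5% in one arm and 15% in the other, with the same true risk in both, gives 9.75% against 9.24% at a true risk of 10% (0.5 point) and 19.5% against 18.5% at 20% (1.0 point). The standard error of a difference with 264 per arm is √(2 × 0.1 × 0.9/264) = 2.6 points at 10% and √(2 × 0.2 × 0.8/264) = 3.5 points at 20%. The spurious difference is therefore about 0.2 to 0.3 of a standard error.

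The handling rule also matters. At p = 15% and L = 20%, counting the lost as recurrence-free gives 13.5%. Leaving out everyone lost before 24 months, including those with an earlier recurrence, returns 15%. Keeping early recurrences but leaving out the event-free losses gives 0.1348 / (0.1348 + 0.85 × 0.80) = 16.5%.

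With complete follow-up the choice of test hardly matters: for 10% against 20%, power is 90% by chi-square and 92% by log rank.

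**The case against.** The other side has good points, and several limit the conclusion.

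- A reader might infer that every secondary endpoint, costs included, is tied to these tests. The article does not support that. *Cost analysis* and *Economic evaluation* plan costs and QALYs separately, and the t test in the list already compares mean costs. No criticism of the cost analysis follows.
- A reader might infer that the admission scores are ignored. That is not established either: *Endpoints* speaks of changes over time, and a t test on change scores uses the baseline. What remains is that this never has smaller variance than ANCOVA, and still takes the visits one at a time.
- Under randomization the unadjusted comparison of quality of life is valid. The admission score is taken during acute illness, so its correlation with scores a year or two later may be low; at 0.3 the gain over follow-up scores is 9%.
- A reader might infer that the recurrence result is biased. Recurrence is defined as a proportion at fixed times, for which chi-square is sound when follow-up is complete. The article gives no 24-month loss, and at 1% the error is negligible. Nor does dropping the lost necessarily bias the result: under independent loss a true completer analysis does not.
- Kaplan-Meier and Cox methods also assume that loss is unrelated to outcome. They correct for unequal loss, but not for patients who leave because of how they are doing.

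What stands is that the listed tests neither adjust, nor join the visits, nor use partial follow-up, and that better methods need no further data.

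**Conclusion.** The point holds as a modest improvement to the secondary analyses, not as an error that threatens the trial. For quality of life the loss is one of precision only: 9% of variance at an assumed correlation of 0.3 and 25% at 0.5, measured against a t test on follow-up scores. For recurrence the bias is conditional. It is at most 0.1 point at 1% loss and about 0.5 to 2 points at 20% loss, for an assumed true risk of 5% to 20%. Unequal loss would add a spurious difference that is small beside the sampling error. Correlation, recurrence risk and 24-month loss are assumptions shown as ranges; none is in the article. Time to full recovery is analysed by other methods and is not touched.

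**What to change.** Replace the single sentence with three short ones:

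1. EQ-5D, SF-36 and GIQLI: a baseline-adjusted model (ANCOVA at a chosen visit, or a mixed model for repeated measures over 3, 6, 12 and 24 months) with the admission score, Hinchey stage and centre as covariates.
2. Recurrence: Kaplan-Meier or cumulative incidence estimates at 12 and 24 months, compared by the log rank test or Cox regression already used for the primary endpoint. State that this assumes non-informative loss, and report loss to follow-up by arm.
3. All other simple, one-time outcomes: the four tests as now listed.

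The change should be made before outcome data are seen. It costs a little more analysis work and needs no new data, visits or patients.
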